## Introduction

The coronavirus disease (COVID)-19 pandemic has caused significant worldwide death and disability, particularly prior to the widespread availability of vaccine. Since the start of the pandemic, there have been seven waves of COVID-19 caused by evolving variants of the Severe Acute Respiratory Syndrome coronavirus-2 (SARS-CoV-2) (1, 2). In Canada, the province of Alberta, a region with 4.5 million inhabitants, has consistently had the highest seroprevalence for SARS-CoV-2 and in November 2023 approximately 85% had evidence for prior infection (3). However, the immediate health risk from acute infection has been low with a hospitalization rate of 5.5% and death in 1% (4).

While the short-term prognosis of COVID-19 is excellent, the intermediate and long-term health risks are of greater concern. A 2022 national survey found that approximately 17% of Canadians with COVID-19 report persistent symptoms lasting greater than 12 weeks, a syndrome referred to as long COVID or post COVID condition (5, 6). Symptoms are often characterized by fatigue, shortness of breath and/or cognitive impairment, with a disproportionate effect in women (5). Among affected individuals, 47% reported symptoms lasting at least 1 year and 21% described symptoms that often or always limited daily activities. The national survey also found that 27% of patient with SARS-CoV-2 developed long COVID following the Alpha variant infection compared to 13% with the Omicron variant (5).

Furthermore, population health studies have shown that COVID-19 confers a 50–70% excess risk of incident cardiovascular disease and diabetes mellitus in the first 12 months (7, 8). These health risks appear greater in patients with long COVID (9). The mechanism(s) responsible for long COVID and the increased cardiometabolic risk are not well understood and there is a lack of high-quality evidence-based studies guiding management.

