Our primary objective was to comprehensively apply multi-system MRI to assess the presence and extent of organ injury (heart, lungs, brain, abdominal viscera and skeletal muscle) among patients with recovered COVID-19 and compare these findings between patients with moderate to severe symptoms, minimal symptoms, and healthy controls without prior infection. As a secondary objective, we also sought to characterize imaging and circulating biomarkers with the potential to exacerbate cardiovascular health. Additionally, we incorporated opportunistic supplementary studies to explore the impact of COVID-19 on energy metabolism and patient’s perspectives.

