### Participant selection

Adult patients within 3 months of COVID-19 illness and prior to the availability of m-RNA vaccination, were recruited from October 2020 to July 2021. Patients with COVID-19 illness requiring hospitalization were identified prospectively at the University of Alberta hospital and retrospectively by the regional health authority, Alberta Health Services. Interested patients with less severe COVID-19 illness also contacted the study team following advertisement on the internet, mainstream media and personal communication. All patients required documentation of COVID-19 infection on nasal or oropharyngeal swab polymerase chain reaction testing within the last 6 months. Healthy controls without prior COVID-19 infection were also recruited from July 2021 to July 2023. Normative brain imaging and cognitive testing were collected separately from healthy control participants prior to the pandemic (19). Control participants with a history of cardiovascular disease or cardiovascular risk factors were excluded. No participants had contraindication to MRI and all provided informed consent after a review of the study objectives, procedures and potential risks and benefits.

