### Statistical plan

The Shapiro–Wilk normality test will be used to test the normal distribution of continuous variables which will be expressed as mean ± standard deviation or median (25th, 75th percentile), as appropriate. Categorical variables will be expressed as frequency and percentage. When comparing data between recovered COVID-19 patients and healthy controls, chi-square testing or Fisher’s exact test will be used for categorical variables and two sample t-test or Mann–Whitney U test used for continuous variables, as appropriate. Functional performance, biomarker results and imaging metrics indicative of organ injury will be compared across groups of symptom severity (none, mild, moderate and severe) within the recovered COVID-19 patients using a one-way analysis of variance with *post hoc* pairwise comparisons by either Tukey’s or Games-Howell tests, depending on equality of variances. Pearson correlation analyses will evaluate relationships between MRI measures of tissue injury and functional performance metrics. Univariable Cox proportional regression of clinical outcome will be performed in all serum and imaging parameters. In the multivariable Cox proportional hazard analysis, all non-collinear parameters of interest with univariable *p*-value < 0.2 will independently test for their association with composite outcome after adjustment for baseline risk. A *p* value less than 0.05 will be considered significant for all tests.

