**COVID-19 Illness**		
Duration of Illness		
1–7 days, (%)	80 (37%)	Not applicable
8–14 days, (%)	68 (32%)	
>14 days, (%)	67 (31%)	
Hospitalized, (%)	59 (27%)	
Intensive care unit, (%)	17 (8%)	
Ventilation, (%)	11 (5%)	

Values are represented as total number (%) or mean (standard deviation).

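### Acute severity is tied to recruitment route and was recorded, yet the planned patient-control, symptom-severity and correlation analyses pool hospitalised and non-hospitalised patients with no term for it

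*Protocol article*

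**What the plan says.** Participant selection gives two entry routes. For severe illness, "Patients with COVID-19 illness requiring hospitalization were identified prospectively at the University of Alberta hospital and retrospectively by the regional health authority". For milder illness, "Interested patients with less severe COVID-19 illness also contacted the study team following advertisement on the internet, mainstream media and personal communication". The article gives no count by route. Table 3 reports 59 of 215 patients (27%) as hospitalised, and the section on medical profile and symptoms confirms that the need for hospitalisation and intensive care was recorded.

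The primary objective in the Introduction is "to assess the presence and extent of organ injury (heart, lungs, brain, abdominal viscera and skeletal muscle) among patients with recovered COVID-19", with comparison between symptom groups and healthy controls. Study outcomes lists symptom burden and organ injury metrics as primary.

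The Statistical plan names the analyses. "When comparing data between recovered COVID-19 patients and healthy controls", it uses two-sample or contingency-table tests. Within patients it uses a one-way ANOVA across four symptom-severity groups, and Pearson correlation between MRI measures and functional performance. None of these has a term for hospitalisation or route. Adjustment for baseline risk is mentioned only for the Cox model of clinical outcome.

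**The concern.** Two features of the plan interact. The routes differ by acute severity, so the share of severe cases in the sample is a product of recruitment. Acute severity also predicts at least one primary imaging measure in the article's own cited evidence: the Sample size calculation section reports higher native myocardial T1 after hospitalisation than after recovery at home (p = 0.008).

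Two consequences follow. First, an unadjusted pooled difference from controls is a weighted average of two possibly different effects, with weights set by how many patients each route supplied. Second, if hospitalised and non-hospitalised patients also differ in how often they have lasting symptoms, an analysis by symptom severity compares groups with different proportions of severe acute illness. A difference in organ injury between symptom groups could then arise, or be masked, without any symptom-injury relation within either severity level. That relation is the study's central hypothesis.

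Symptom burden is a primary outcome as well. Where entry depends on volunteering, its frequency in the sample need not match that among recovered patients in general.

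**Working it through.** **Inputs from the article**
- Table 3: 59 hospitalised of 215 patients, so 215 − 59 = 156 not hospitalised; 133 controls.
- Introduction: 5.5% hospitalised after infection, with no period given; long COVID in about 17% in a 2022 national survey (27% after Alpha, 13% after Omicron).
- Sample size calculation: in one cited study, median T1 of 1,082 ms in controls, 1,125 ms in all patients, 1,141 ms in hospitalised (33) and 1,119 ms in home-recovered patients (67).

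**Step 1. Reproduce the stated share.** 59/215 = 27.4%, matching the printed 27% (95% Wilson interval 21.9% to 33.8%). Against 5.5% this is a ratio of 27.4/5.5 = 5.0, if 5.5% is the right comparator.

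**Step 2. Effect of the mix on the patient-control difference.** With hospitalised share h, and medians used as if they were means:

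difference(h) = 1,119 + h × (1,141 − 1,119) − 1,082 = 37 + 22h ms

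- Check at the cited study's own mix, h = 0.33: 1,119 + 7.3 = 1,126.3 ms, against its reported overall median of 1,125 ms. The approximation is adequate for illustration.
- This cohort, h = 0.274: 43.0 ms.
- h = 0.055: 38.2 ms.
- Shift: 4.8 ms, and 4.8/38.2 = 13%. The share that remains is 38.2/43.0 = 89%.

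**Step 3. Effect on the symptom-injury contrast.** Assume no relation between symptoms and T1 within either severity level. The pooled contrast is then 22 ms × (hospitalised share among symptomatic − hospitalised share among non-symptomatic). The article gives no symptom data by hospitalisation, so two assumed patterns are shown:
- 27% of hospitalised and 45% of non-hospitalised symptomatic. Symptomatic: 15.9 of 86.1 hospitalised (18.5%). Non-symptomatic: 43.1 of 128.9 (33.4%). Artefact: 22 × (0.185 − 0.334) = −3.3 ms.
- 50% and 29%. Symptomatic: 29.5 of 74.7 (39.5%). Non-symptomatic: 29.5 of 140.3 (21.0%). Artefact: 22 × (0.395 − 0.210) = +4.1 ms.

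The artefact is small for T1, but its sign depends on the pattern of recruitment, and a one-way ANOVA cannot separate it from a real association.

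**Step 4. Symptom frequency among volunteers.** If a symptomatic mild case is k times as likely to volunteer (k is assumed) and the true share is p, the share among volunteers is kp/(kp + 1 − p). For k = 1, 2, 3, 5:
- p = 17%: 17%, 29%, 38%, 51%.
- p = 27%: 27%, 43%, 53%, 65%.

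The documents do not say which k applies; k = 1 means no distortion.

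**Step 5. Cost of stratifying.** With a common standard deviation and all participants contributing, interval width is proportional to √(1/n₁ + 1/133):
- Pooled 215: 0.110.
- 156 non-hospitalised: 0.118, about 7% wider.
- 59 hospitalised: 0.156, about 42% wider.

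Reweighting to 5.5% would use weights 0.055/0.274 = 0.20 and 0.945/0.726 = 1.30. The effective number of patients is 215²/(59 × 0.2004² + 156 × 1.3024²) = 173.

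**The case against.** The strongest reply is that this is a study of association and comparison, not of prevalence. The stated aim compares organ injury between symptom groups, with controls and against function; no section promises an estimate representative of Alberta. Oversampling severe illness is an ordinary way to obtain a spread of severity. Moreover, volunteering that depends on symptoms changes the size of the symptom groups but need not change mean injury within them. All of this stands. It disposes of any complaint that the sample is unrepresentative in itself. It does not answer confounding by acute severity, which acts on the association the study does claim to estimate.

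The benchmarks are also weak. The 5.5% has no stated period, while the cohort comes from the first two waves and was unvaccinated. The T1 illustration rests on one study. A second study cited in the same section, of 148 patients all previously hospitalised, found an excess over controls of only 1,033 − 1,008 = 25 ms, less than the 37 ms used here for home-recovered patients. The millisecond figures therefore cannot be taken as estimates for this cohort.

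A reader might also infer that hospitalised patients entered regardless of symptoms, that people without symptoms are scarce, or that all 156 non-hospitalised patients answered advertisements. The article states none of these. Hospitalised patients also had to consent and attend, Table 3 has no symptom data, and route counts are not reported.

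Finally, stratified reporting could sit in an analysis plan that is not shown. However, the article does fix the primary tests, and as fixed they pool.

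**Conclusion.** The point holds in a limited form. Acute severity is recorded and linked to recruitment route, and the article's own cited data relate it to a primary imaging measure. It is uncontrolled in the planned patient-control tests, the symptom-severity ANOVA and the correlations. The pooled contrast therefore depends partly on the recruitment mix, and the symptom-injury association may be confounded.

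On the cited T1 values the mix accounts for about 5 of 43 ms. This assumes that medians behave as means, that one cited study carries over, and that 5.5% is a fair comparator. The confounding artefact was between about −3 and +4 ms in the two assumed patterns; its size for other organs cannot be computed from the documents.

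A reader might go further and conclude that the reported organ injury reflects recruitment rather than recovered COVID-19. The documents do not support that: in the same illustration 38 of 43 ms remains after the mix is changed. Nor do they show that symptom burden is overstated; that depends on an unknown volunteering ratio.

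**What to change.** Keep the pooled analyses and add the following:
- Report each primary patient-control comparison separately for the 59 hospitalised and the 156 non-hospitalised patients.
- Run the symptom-severity and MRI-function analyses adjusted for, or stratified by, hospitalisation (for example, a linear model with symptom group and hospitalisation, and partial or within-stratum correlations).
- State that symptom frequency in this recruited sample is not to be interpreted as a prevalence.

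Standardising to 5.5% is at most an optional sensitivity analysis: the period of that rate is not given, and reweighting does not remove self-selection among those who came forward.

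No new data are needed, because hospitalisation was recorded. The cost is analysis and reporting effort, and wider intervals within strata, chiefly among the 59 (about 42% wider than pooled, under the assumptions shown). Splitting the 59 further across four symptom groups would leave small cells, so adjustment may be more practical than full stratification there.

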## Methods and analysis

### Study design

This is an observational prospective case–control study of patients in Alberta with recovered COVID-19 from the first 2 waves of the pandemic and age- and sex-matched healthy control participants without prior COVID-19 infection. Institutional approval was obtained from the health research ethics boards at the University of Alberta for the study of patients with recovered COVID-19 (Pro00102389), the two supplementary studies (Pro00109391, Pro00110221) and the healthy controls (Pro00110706) and at the University of Calgary for patients with recovered COVID-19 (REB21-0035). The study was also registered at clinicaltrials.gov (MOIST late cross-sectional study; NCT04525404). All patients provided written informed consent. The Canadian VIGOUR Centre (thecvc.ca) helped provide project management, and the study team vouches for the data integrity and analyses of the study. Patient related variables were captured in REDCap (Research Electronic Data Capture) hosted at the University of Alberta and imaging data was stored in a secure server in the department of biomedical engineering at the University of Alberta. The principal investigator ([name]) oversaw site monitoring and data management and will supervise all analyses related to the study.

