### Study outcomes

Primary outcomes include patient reported symptom burden and organ injury metrics as assessed by functional performance evaluations, serum biomarkers and MRI tissue characterization (Table 1). Secondary outcomes include imaging and circulating biomarkers of cardiovascular health (Table 2). Clinical events at 12 months will be collected though chart review to ascertain relevant clinical outcomes including incident diabetes and cardiovascular disease.

**Table 1 tab1:** Summary of organ injury outcomes.

Organ	Functional performance	Circulating biomarkers	Magnetic resonance
LUNG	Spirometry 6 min walk testing	None	Lung water density Lung lesions (radiomic analysis)
CARDIAC	6 min walk testing	Troponin I B-type natriuretic peptide	LVEF Myocardial T1 Myocardial T2
BRAIN	Cognitive testing	None	Brain volume Brain lesions (FLAIR and DTI) Susceptibility and iron mapping
HEPATIC	None	AST ALT GGT LDH Total bilirubin	Hepatic T1 Hepatic T2*
RENAL	None	Electrolytes Creatinine	Renal T1
SKELETAL MUSCLE	6 min walk testing	None	Skeletal muscle T1 Skeletal muscle T2*

AST, aspartate aminotransferase; ALT, alanine aminotransferase; LDH, lactate dehydrogenase; GGT, gamma-glutamyl transferase; LVEF, left ventricular ejection fraction; FLAIR, fluid attenuation inversion recovery; DTI, diffusion tensor imaging.

**Table 2 tab2:** Summary of cardiovascular health outcomes.

	Circulating biomarkers	Magnetic resonance	Clinical events
CARDIAC	Troponin I B-type natriuretic peptide	LVEF Myocardial T1 Myocardial T2	Cardiovascular death or hospitalization
CARDIOMETABOLIC	C-reactive protein White blood cell count Glucose Insulin Lipid profile	Visceral adipose tissue Hepatic fat Intramuscular fat Intermuscular fat	Incident diabetes Incident dyslipidemia Incident hypertension

LVEF, left ventricular ejection fraction.

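### Cardiovascular disease and risk factors were excluded in controls only, so the planned unadjusted patient-control tests of cardiac and cardiometabolic markers cannot separate infection from baseline risk

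*Protocol article*

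**What the plan says.** All references are to the protocol article.

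- **Controls** (Participant selection): "Control participants with a history of cardiovascular disease or cardiovascular risk factors were excluded". The section does not list which risk factors count.
- **Patients** (same section): "All patients required documentation of COVID-19 infection on nasal or oropharyngeal swab polymerase chain reaction testing within the last 6 months". No cardiovascular or risk-factor exclusion is stated for them.
- **Matching** (Study design): the comparison group is described as "age- and sex-matched healthy control participants without prior COVID-19 infection". Cardiovascular risk is not a matching factor.
- **Objectives** (end of the Introduction): the primary objective is to measure organ injury and "compare these findings between patients with moderate to severe symptoms, minimal symptoms, and healthy controls without prior infection".
- **Outcomes** (Study outcomes): Table 1 counts troponin I, BNP, left ventricular ejection fraction (LVEF) and myocardial T1 and T2 as organ injury, a primary outcome. "Secondary outcomes include imaging and circulating biomarkers of cardiovascular health". Table 2 repeats the cardiac markers and adds glucose, insulin, lipids and visceral, hepatic and muscle fat.
- **Tests** (Statistical plan): the patient-control comparison is to be made by "two sample t-test or Mann–Whitney U test used for continuous variables, as appropriate". Proportions get a chi-square or Fisher's exact test. The only adjustment named in that section belongs to the Cox model of clinical outcome.

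**The concern.** The exclusion acts on one group only, and it acts on the outcomes or their direct determinants. Removing people with diabetes or dyslipidemia from the controls cuts off the upper end of glucose and lipids in that group alone. Removing hypertension and cardiac disease bears on LVEF, BNP and myocardial T1 in the same way. An unadjusted test then returns the sum of any infection effect and the difference in baseline risk, with no means of telling them apart. The primary objective is exposed as well as the secondary one, because the cardiac markers sit in Table 1 and that objective names the controls. The Discussion hopes that the results will point to treatment targets, including for post-COVID cardiovascular risk, so a misread contrast would matter.

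**Working it through.** **1. Reproduce Table 3** (215 patients, 133 controls; every control count below is 0).

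| Condition | Patients | Stated | Recomputed |
|---|---|---|---|
| Hypertension | 51 | 24% | 51/215 = 23.7% |
| Diabetes | 28 | 13% | 28/215 = 13.0% |
| Dyslipidemia | 38 | 18% | 38/215 = 17.7% |
| Coronary artery disease | 4 | 2% | 4/215 = 1.9% |

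The stated figures reproduce. The standardized difference is (p1 − p0)/√{[p1(1 − p1) + p0(1 − p0)]/2}. It gives 0.79 for hypertension, 0.66 for dyslipidemia and 0.55 for diabetes. The stated matching factors also differ: mean age 51 v 47 years, and 65% v 51% female.

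**2. Share of patients with at least one of the three conditions.** Table 3 does not give the overlap, so only bounds are possible.
- Full overlap: 51/215 = 23.7%.
- No overlap: (51 + 28 + 38)/215 = 117/215 = 54.4%.
- Controls: 0%.

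**3. What this could do to an unadjusted test (illustration).** Assume no COVID-19 effect, unit SD in both groups, a two-sided 5% test, and a marker that is d SD higher in people with a risk factor. The document gives no value of d. The spurious shift is prevalence × d, and its standard error is √(1/215 + 1/133) = 0.110.

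| Assumed d | Rejection probability at 23.7% | Rejection probability at 54.4% |
|---|---|---|
| 0.25 | 8% | 23% |
| 0.5 | 19% | 69% |
| 0.8 | 41% | 98% |
| 1.0 | 58% | over 99% |

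**4. Cost of restricting the patients.** Remove hypertension, diabetes, dyslipidemia and cardiovascular disease (coronary disease 4, heart failure 1, atrial fibrillation 4, stroke 5).
- Full overlap: 215 − 51 = 164 remain.
- No overlap: 215 − (51 + 28 + 38 + 4 + 1 + 4 + 5) = 215 − 131 = 84 remain.

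The detectable difference at 80% power is 2.80 × √(1/n + 1/133).
- n = 215: 0.31 SD.
- n = 164: 0.33 SD.
- n = 84: 0.39 SD.

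**5. If smoking counts as a risk factor.** Table 3 lists 9 current and 50 past smokers among patients, and 1 and 8 among controls. Excluding any smoking history from both groups (taking current and past as separate people) leaves 133 − 9 = 124 controls. At least 9 + 50 = 59 and at most 131 + 59 = 190 patients would leave, so 156 to 25 remain. The detectable difference is then 2.80 × √(1/156 + 1/124) = 0.34 SD to 2.80 × √(1/25 + 1/124) = 0.61 SD.

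**6. Would covariate adjustment for these conditions do instead?** No control has hypertension, diabetes or dyslipidemia. In a model with those terms, controls carry information only about patients without the condition. Any statement about patients who have it would be extrapolation.

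**The case against.** The strongest reply has four parts.

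- *Healthy controls are a deliberate and openly stated choice, recruitment is over, and an adjusted analysis may sit in an analysis plan that is not shown.* The first two parts are true, but disclosure does not remove confounding. The article does not leave the test open either: it names unadjusted tests for this contrast.
- *Much of the study does not use the controls.* This stands. Comparisons across symptom severity, correlations between MRI and function within patients, and the Cox models of clinical events are untouched by this point. The secondary objective speaks only of characterizing biomarkers and does not itself name a control contrast.
- *The imbalance has other sources.* This stands in part. The stated exclusion names neither COPD nor weight. The absence of COPD in controls and the 11 kg weight gap (83 v 72 kg) may reflect how each group was recruited; 27% of patients had been hospitalized. False-positive rates built on an assumed correlation with weight would not measure the effect of this exclusion.
- *Restriction has biases of its own.* This also stands. The Introduction cites excess incident diabetes and cardiovascular disease after infection, so excluding patients on their status at the study visit could remove cases that infection caused. Adjusting fat, glucose or insulin for BMI could remove part of the outcome. Both points shape the fix.

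A reader might go further and infer that any patient-control difference is produced by eligibility and not by infection. The documents do not support that. No results are given, and the design shows only that the two sources cannot be separated.

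**Conclusion.** The concern holds for patient-control contrasts of cardiac and cardiometabolic markers: all of Table 2's biomarkers and imaging, and troponin, BNP, LVEF and myocardial T1/T2 in Table 1. For these, the plan as written confounds infection with baseline risk. Between 23.7% and 54.4% of patients, against 0% of controls, have hypertension, diabetes or dyslipidemia. That rests on the stated exclusion, Table 3 and the named tests, and on no assumed value. The probability of a spurious significant result does rest on assumptions: across the values of d tried it runs from 8% to over 99%, so no single false-positive rate should be quoted as a property of this study. The point does not extend to within-patient analyses.

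**What to change.** In the Statistical plan, for patient-control contrasts of these outcomes:

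1. Make the main analysis an age- and sex-adjusted comparison restricted to patients who met the controls' cardiovascular and risk-factor criteria **before infection**. The article says that health records were reviewed; whether they date each condition relative to infection has to be confirmed.
2. List the risk factors that count, and apply the same smoking rule to both groups.
3. Show results with and without BMI adjustment. Do not take the BMI-adjusted result as the main one for visceral, hepatic or muscle fat, glucose or insulin.
4. Report the full-cohort unadjusted contrast as descriptive, without attributing it to COVID-19.
5. Keep the within-patient analyses as planned.

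**Cost.** No new participants or measurements, but the dates of onset must be drawn from records. On hypertension, diabetes, dyslipidemia and cardiovascular disease alone, 51 to 131 of 215 patients leave this contrast and the detectable difference rises from about 0.31 to 0.33-0.39 SD. The loss is larger if smoking history counts. These figures use history as tabulated; conditions that arose after infection would not count, so fewer would leave. The result applies only to patients without prior risk factors.
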